#### Blinding

Pharmacists will be blind to allocation status until the point at which they open the sealed envelope. Thereafter they are not involved in research data collection. For the purposes of both follow-up study and data management relevant personnel will be blinded to randomisation status throughout the trial.

#### Statistical methods

The data will be analysed on an intention to treat basis. For outcome measures t-tests or Mann–Whitney tests will be used for continuous data and chi-square tests used for categorical data. If possible confounding is identified, ANCOVA and logistic regression will be used to examine the effect of the interventions over and above these other factors, and effect sizes and odds ratios calculated. For all tests, if necessary, measures will be transformed before analysis. All analyses not conforming to an *a priori* statistical plan will be declared as exploratory.

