#### Selection criteria

People aged 18 years or over accessing pharmacy services within the participating pharmacies located in NHS Hammersmith and Fulham who: a) have AUDIT scores between 8–19 inclusive; b) are contactable by phone during the study; c) have a home address in the UK; and d) are able to speak, read and write in English are eligible to take part in the study. Excluded are those who are: a) currently in treatment for alcohol problems; b) currently involved in any other alcohol research; and c) employees of the trial pharmacies.

Pharmacy customers will thus be excluded if they are identified as being possibly alcohol dependent (AUDIT score ≥ 20). This group will be advised to see their GP and be given a letter, with their AUDIT assessment result, to take to their GP. Pharmacy customers who are identified as low risk drinkers (AUDIT ≤ 7) will also be excluded from the study. Both excluded groups will be given, “Units and You” booklet
[25], a “Unit/Calorie Calculator Wheel”
[26] and an alcohol services leaflet developed for the study to take away.

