### Outcomes

#### Primary outcomes

● Change in AUDIT scores between trial recruitment and follow-up.

● Proportion of hazardous and harmful drinkers (scoring 8 or higher on AUDIT) at follow-up.

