#### Data collection

Additional trial web pages have been developed and incorporated into the existing online system for pharmacists to record trial data
[31]. The research team will have access to trial data by using secure usernames and passwords created for the trial. This online system has several advantages over the paper-pen method. RD will have access to pharmacy participants’ details as soon as each participant is randomised and the visit to the pharmacy completed; this will allow follow-up telephone calls to be made promptly and avoid delays caused by physically collecting completed trial paperwork from pharmacies. Access to randomisation status and baseline data is prevented. The system requires pharmacists to complete all fields correctly before proceeding to the next step, ensuring trial data are complete. Data can also be accessed without revealing randomisation status.

RD will arrange two telephone calls with study participants. During both calls the researcher will be blind to the participants’ intervention condition. The first telephone call will be made within two weeks of recruitment and will take between two to three minutes to complete. The purpose of this call will be to make personal contact to confirm contact details, gather additional tracing information as necessary and to arrange the follow-up study telephone call three-months post randomisation. Structured interview schedules will be used to ensure all participants are asked the same questions in a consistent manner in both calls. The primary and secondary outcomes specified above will be collected in the follow-up study telephone call after three months. This will take approximately 15 minutes to complete and participants will receive £10 gift voucher as a token of appreciation for completing the second call.

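### Baseline adjustment of the primary outcomes depends on confounding being found, an unsound trigger in a randomised trial that gives up precision a prespecified ANCOVA would keep

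*Protocol article*

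**What the plan says.** All places are in the protocol article.

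- **Primary outcomes** lists two: "Change in AUDIT scores between trial recruitment and follow-up" and "Proportion of hazardous and harmful drinkers (scoring 8 or higher on AUDIT) at follow-up".
- **Statistical methods** sets the default tests: "For outcome measures t-tests or Mann–Whitney tests will be used for continuous data and chi-square tests used for categorical data". None of these has a covariate.
- The same section then states when a model is used: "If possible confounding is identified, ANCOVA and logistic regression will be used to examine the effect of the interventions". The sentence goes on to say that the effect is examined beyond those other factors. It does not say how confounding would be identified, which factors are candidates, or which result is primary if the two differ.
- Rescaling is also conditional: "For all tests, if necessary, measures will be transformed before analysis".
- The section closes with a safeguard: "All analyses not conforming to an *a priori* statistical plan will be declared as exploratory".
- **Selection criteria** requires that participants "have AUDIT scores between 8–19 inclusive", so a baseline AUDIT exists for everyone randomised. **Data collection** adds: "The system requires pharmacists to complete all fields correctly before proceeding to the next step, ensuring trial data are complete".

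**The concern.** Allocation is random, within blocks of 12 for each pharmacist. Unless concealment fails, any baseline difference between arms is a chance event and not confounding in the usual sense. The reason to adjust is that a covariate predicts the outcome. That is known in advance for baseline AUDIT and does not depend on how the arms happen to look.

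Two things are at stake.

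- **Precision.** For the continuous outcome, a change score uses baseline by subtraction, which fixes its slope at 1 whatever the true slope is. For the binary outcome, baseline is not used at all. Yet the threshold of 8 is also the entry floor, so a person entering at 8 and a person entering at 19 plainly have different chances of finishing below it.
- **Sensitivity to chance imbalance.** If the intervention arm happens to start higher and the true slope is below 1, its change score will tend to look better without any treatment effect. Adjustment that waits for an undefined signal may or may not correct this.

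**Working it through.** **1. The plan's own figure.** Inputs from Sample size: standardised effect 0.30, one-tailed alpha 0.05, power 80%. An exact two-sample t calculation gives 139 per group (power 80.2%). Then 139 / 0.70 = 198.6, so 199 per group and 398 in total. The stated figures reproduce. The calculation has no baseline term, and the section does not say whether 0.30 is in SDs of the follow-up score or of the change.

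**2. Variance formulas.** Let s0 and s1 be the baseline and follow-up SDs and ρ their correlation. None of these is in the document, so all are assumptions.

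- Change score: Vc = s0² + s1² − 2ρ·s0·s1
- ANCOVA: Va = s1²(1 − ρ²)
- Difference: Vc − Va = (s0 − ρ·s1)², which is never negative. It is zero only when the slope ρ·s1/s0 equals 1.

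**3. Equal SDs.** Va/Vc = (1 − ρ²) / [2(1 − ρ)] = (1 + ρ)/2. The last two columns give power at 139 per arm if 0.30 is in follow-up SD units.

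| ρ | Va/Vc | Variance reduction | Power, change score | Power, ANCOVA |
|---|---|---|---|---|
| 0.3 | 0.65 | 35% | 68% | 84% |
| 0.5 | 0.75 | 25% | 80% | 89% |
| 0.7 | 0.85 | 15% | 94% | 97% |

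**4. Restricted entry range.** Selection to 8–19 compresses s0 relative to s1, so equal SDs is the optimistic case. For ρ of 0.3, 0.5 and 0.7:

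- s0/s1 = 0.8: Va/Vc = 0.784, 0.893 and 0.981
- s0/s1 = 0.5: Va/Vc = 0.958, 1.000 and 0.927

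Simulating a population selected to 8–19 on baseline, with reliability 0.5 to 0.8 and follow-up SD about 4 to 4.5, gives ratios of 0.88 to 0.965. That is roughly 4–12% lower variance.

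If 0.30 is in change-score SD units, the non-centrality at 139 per arm is 0.30 × √(139/2) / √(Va/Vc). It is 2.50 at ratio 1, 2.55 at 0.96 and 2.67 at 0.88. Exact one-tailed power is 80.2%, about 82% and about 84%.

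**5. Error rate.** Null simulation: 20,000 trials per setting, 139 per arm, one-sided 5%, equal SDs.

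| Rule | ρ = 0.3 | ρ = 0.5 | ρ = 0.7 |
|---|---|---|---|
| Change-score test always | 4.9% | 5.0% | 4.9% |
| ANCOVA always | 4.8% | 4.8% | 4.8% |
| ANCOVA only if baseline differs at p < 0.05 | 4.3% | 4.4% | 4.7% |
| Either result may be claimed | 7.3% | 7.0% | 6.4% |
| Change-score test, intervention arm high at baseline by chance (z > 1.28) | 24% | 19% | 14% |
| ANCOVA in those same trials | 5.4% | 5.0% | 4.8% |

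The p < 0.05 trigger is only an illustration, since the protocol states no threshold. With a true effect of 0.30 follow-up SDs it recovers little power: 69% against 83% for fixed ANCOVA at ρ = 0.3, and 81% against 89% at ρ = 0.5. The figures under chance imbalance would be smaller with a compressed baseline SD, because the term at work is the gap between the true slope and 1, multiplied by the imbalance.

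**The case against.** The strongest reply has four parts.

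- **The default tests are valid under randomisation.** This stands. A reader might infer that the conditional rule inflates the 5% error rate. The document does not support that: a strict imbalance trigger is slightly conservative, and inflation to 6–7% needs freedom to claim either result, which the protocol does not grant.
- **The conditional sentence can be read as a supplementary check.** On that reading the default test stays the headline result, and a separate plan, to which the closing safeguard points, fixes covariates and triggers. The reading is fair, and for this reason the choice between t-test, Mann–Whitney and transformed scales is not pressed here. It does not remove the point: the article states a trigger, the trigger is unsound, and adjustment made under it would be part of the stated plan.
- **The change score already uses baseline.** This is correct for the continuous outcome. To say that baseline AUDIT is thrown away would be true only of the binary one.
- **The gain is modest.** With the restricted entry range this is so, and in some configurations it is nil.

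Two other tempting arguments also fail. Selection to 8–19 does not itself push the slope below 1: in simulation the slopes were 0.50, 0.65 and 0.80 both before and after selection, equal to the assumed reliabilities. And no rate can be given for how often the trigger would fire, because the article lists no screening variables and no threshold.

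**Conclusion.** The point holds as a recommendation on efficiency and prespecification, not as a finding of invalidity. The stated rule makes adjustment depend on a search that means little in a randomised trial, and it leaves open which result is primary.

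The likely cost is a residual variance about 4–12% higher than it need be, taken relative to the change-score variance, or 2 to 4 percentage points of power if 0.30 is in change-score SD units. The cost is larger (15–35% of variance) only if the baseline and follow-up SDs are about equal and the correlation lies between 0.7 and 0.3. All of this rests on assumed correlations and SDs. The gain for the binary outcome was not quantified.

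A reader might also infer that the trial falls short of its stated power. This point does not show that: 139, 199 and 398 reproduce for the stated one-tailed calculation, and the SD scale of the 0.30 is not given.

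**What to change.** - Delete the trigger that makes adjustment depend on confounding being found.
- Make ANCOVA of three-month AUDIT on arm and baseline AUDIT the single primary analysis of the continuous outcome, reporting the adjusted mean difference with its confidence interval.
- Analyse AUDIT of 8 or more by logistic regression on arm and baseline AUDIT. State that the odds ratio is conditional on baseline, so it is a different quantity from the one behind the chi-square comparison, and also report the standardised risk difference or the raw proportions.
- Pharmacist, the blocking factor in Randomisation, may be added to both models.
- Keep the t-test, Mann–Whitney and chi-square tests as supportive analyses.

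The cost is a few sentences, plus the explicit statement of what the odds ratio measures. No new data are needed. The sample size can stay, since ANCOVA keeps or raises its power.

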#### Sub-study

Participants who have consented to participate in a sub-study, on their experience of participating in the trial, will be randomly selected to be telephoned (*N* = 24). Consent for this will be obtained alongside consent to participate in the trial, i.e. in the consultation room with the pharmacist. They will be contacted approximately one month after the three-month follow-up telephone call by RD for a 20 minute discussion by telephone. A semi-structured topic guide developed for the study will be used to explore participants’ experience. The telephone interviews will be recorded using a digital voice recorder, transcribed verbatim, data managed using a qualitative research program
[32] and analysed. Those who have completed the telephone interview will be sent a £10 gift voucher as a token of appreciation for participation.

#### Ethical and research governance approval

This study has been given a favourable ethical opinion (on 12^th^ December 2011, REC reference: 11/LO/1448) by the NRES Committee London- Queen Square, UK. NHS Permission was granted by The West London Primary Care Consortium (for Research and Innovation) on behalf of NHS Hammersmith and Fulham (Primary Care Trust) on 19^th^ March 2012, NIHR CSP number: 11839.

## Discussion

The UK Department of Health’s stated aim is to involve community pharmacists in the delivery of BI to reduce alcohol harms
[3]. This will be the first RCT study to assess the effectiveness of BI delivered by community pharmacists and given this policy context, it is pragmatic in design. This setting attracts hazardous and harmful drinkers who are accessing community pharmacy services. There are minimal exclusion criteria, for example by not excluding those with co-morbidities, so the study population is similar as possible to those BIs would be delivered to if found to be effective.

The time available for pharmacists’ training (a morning on trial procedures and an afternoon on BI delivery with additional provision for a two hour evening follow-up) was negotiated mindful of time pressures and other commitments. Pharmacists will be reimbursed for their one day of training, and given a modest fee given for each trial participant. Similarly the duration of the BI has been tailored to the time available for interventions delivery in community pharmacies.

One possible consequence of these study design decisions is that a null finding may result because the effect of BI has been diluted by these study characteristics. We do not anticipate that setting-specific factors will interfere with intervention conduct, and the capacity of pharmacists to deliver BIs effectively is what we are studying. Although the primary care evidence-base is well established, there are many important questions about BI effectiveness that remain to be addressed
[33,34]. An evaluation of a stronger intervention or with more extended training and skills development inputs may show greater effectiveness and an efficacy trial may show more promise. We are aware of these possibilities and have made our study design decisions as we judge most appropriate in the policy context described. If the trial produces evidence of effectiveness then it will be appropriate to subsequently undertake a large multi-centre trial evaluating the effectiveness and cost-effectiveness of this BI model to inform decision-making about the delivery of BIs in pharmacies nationally.

## Abbreviations

ANCOVA: Analysis of covariance;AUDIT: Alcohol Use Disorder Identification Test;BI: Brief Intervention;CLRN: Comprehensive Local Research Network;NHS: National Health Service;NIHR CSP: National Institute of Health Research Co-ordinated System for obtaining National Health Service Permission;NRES: National Research Ethics Services;REC: Research Ethics Committee;SASQ: Single Alcohol Screening Question;UK: United Kingdom;UKCRN: United Kingdom Central Research Network;W.H.O: World Health Organisation
